## Abstract

**Background:**

Many patients with type 2 diabetes (T2DM) are not able to reach the glycaemic target level of HbA1c < 7.0%, and therefore are at increased risk of developing severe complications. Transition to insulin therapy is one of the obstacles in diabetes management, because of barriers of both patient and health care providers. Patient empowerment, a patient-centred approach, is vital for improving diabetes management. We developed a web-based self-management programme for insulin titration in T2DM patients. The aim of our study is to investigate if this internet programme helps to improve glycaemic control more effectively than usual care.

**Methods/Design:**

T2DM patients (n = 248), aged 35–75 years, with an HbA1c ≥ 7.0%, eligible for treatment with insulin and able to use the internet will be selected from general practices in two different regions in the Netherlands. Cluster randomisation will be performed at the level of general practices. Patients in the intervention group will use a self-developed internet programme to assist them in self-titrating insulin. The control group will receive usual care.

Primary outcome is the difference in change in HbA1c between intervention and control group. Secondary outcome measures are quality of life, treatment satisfaction, diabetes self-efficacy and frequency of hypoglycaemic episodes. Results will be analysed according to the intention-to-treat principle.

**Discussion:**

An internet intervention supporting self-titration of insulin therapy in T2DM patients is an innovative patient-centred intervention. The programme provides guided self-monitoring and evaluation of health and self-care behaviours through tailored feedback on input of glucose values. This is expected to result in a better performance of self-titration of insulin and consequently in the improvement of glycaemic control. The patient will be enabled to 'discover and use his or her own ability to gain mastery over his/her diabetes' and therefore patient empowerment will increase. Based on the self-regulation theory of Leventhal, we hypothesize that additional benefits will be achieved in terms of increases in treatment satisfaction, quality of life and self-efficacy.

**Trial registration:**

Dutch Trial Register TC1316.

## Background

The prevalence and incidence of type 2 diabetes mellitus (T2DM) is high and the number of persons with T2DM is growing rapidly to be 366 million in 2030 [1]. International guidelines recommend tight glycaemic control, in order to prevent the onset or to reduce the progression of complications associated with T2DM [2-5]. However, achieving tight glycaemic targets represents a major challenge. A Dutch study found that at least 30 percent of T2DM patients under care of General Practitioners (GPs) do not achieve good glycaemic control [6].

Insulin therapy should be started when other therapies fail to reach the glycaemic target of HbA1c < 7.0% [5]. Nonetheless, both patients and health care providers often appear reluctant to start insulin therapy [7-9]. GPs largely do not feel familiar with the perceived complexity of the insulin treatment regimen or they think it is too time consuming [7,8]. Patients as well as health professionals fear negative side effects like weight gain and hypoglycaemia feeding into "psychological insulin resistance", causing unwanted delay of insulin initiation [9]. Therefore, it is important to develop tools that facilitate the transition to insulin therapy with subsequent positive effects on glycaemic control. Interactive Behaviour Change Technology (IBCT), including the use of hardware and software to promote and sustain behaviour changes, could provide such a tool [10], and make the titration of insulin become easier for both the patient and the health care provider. Moreover, a patient-driven insulin titration has already proven to be successful [11]. With IBCT in the form of an internet programme, self-titration (i.e. self-monitoring of blood glucose and self-adjustment of insulin dose) could be further facilitated.

### Web-based diabetes management

IBCT is one potential resource for improving diabetes management. In general it assists patients and their clinicians in monitoring changes in health and self-care needs. Secondly, it supports patients' efforts to make behaviour changes by promoting health and effective self-care, and thirdly it enhances communication between patients and potential supports for their disease management. IBCT increases patients' access to the types of services available from their health care team [10].

Several reviews about utilization of IBCT applications to improve care of chronic illness have been published, and these generally have been positive [10]. A systematic review assessing the effects of IBCT for people with a chronic disease found that IBCTs appeared to improve users' knowledge, social support, health behaviours, self-efficacy (a person's belief in their capacity to perform specific skills in a specific situation) and clinical outcomes [12]. However, the included studies involved different IBCTs with different characteristics, for a wide range of chronic diseases.

The use of IBCT in diabetes care has been mainly focussed on the improvement of glycaemic control. Several studies found promising results making use of different aspects of the opportunities of IBCT: improving communication and computerized educational programs [13,14], or making use of a web-based glucose monitoring system [15-19]. A meta-analysis of 16 studies in which home glucose records were used to perform computer-assisted insulin dose adjustment by clinicians showed a significant improvement of HbA1c [20]. To our knowledge, computer-assisted insulin self-titration has not yet been studied in (previous insulin-naive) T2DM patients. In addition, the causal pathways between supposed improved outcomes and IBCT applications in diabetes care remained unclear, because of lack of clarity in how technological innovations of IBCTs were defined and how their impact was measured [21]. In this study we will investigate the use of an IBCT application in T2DM patients based on a theoretical framework for a better understanding and interpretation of the outcomes.

### Theoretical background

The self-titration of insulin supported by an internet programme is based on the patient empowerment approach, defined as 'helping people to discover and use their own ability to gain mastery over their diabetes' [22]. The key element of patient empowerment in diabetes is to facilitate self-management [22,23]. Diabetes outcomes are largely dependent on the daily self-care activities of the patient [24-26]. Empowering patients to better understand and self-manage their diabetes therefore is key, to achieve satisfactory diabetes outcomes, quality of life, satisfaction with treatment and better communication with caregivers [27-29]. The benefits for the caregivers are an increased satisfaction in work, and achievement of treatment goals [29].

Building on the patient empowerment approach, we developed the content and process of our study guided by the principles of the self-regulation theory. This theory was elaborated by Leventhal and colleagues and it proposes that individuals will use strategies that are based on the understanding of their illness and new experiences [30,31]. The theory delineates five core dimensions of illness representations (peoples' perceptions of and beliefs about an illness): identity, cause, timeline, consequences and controllability of the disease in terms of prevention and cure. Through experience and feedback mechanisms, perceptions can be influenced [32]. Web-based support programmes can provide instant and constructive feedback. Illness perceptions could change and confidence and autonomy could increase. Higher self-efficacy beliefs and higher control perceptions are associated with better metabolic control [33].

In our study we will investigate a patient-centred internet intervention supporting self-titration of insulin therapy in T2DM patients. The internet programme will promote self-regulatory behaviour by effective self-monitoring and evaluation of self-care behaviours through feedback on input of the patients' glucose values. This is expected to result in improved self-management skills, self-efficacy and subsequent glycaemic control. Successful self-regulation of diabetes is expected to translate into better quality of life and treatment satisfaction compared to the control group, where there is less emphasis on patients' self-management.

### Objectives

The primary objective of the study is to determine the effect on glycaemic control (HbA1c) of a patient-centred web-based insulin-titration programme in suboptimal controlled T2DM patients starting insulin treatment.

Secondary objectives are to assess the effects of the intervention on frequency of hypoglycaemic episodes, illness perceptions, self-efficacy, treatment satisfaction, and quality of life.

## Methods/Design

### Design of the study

The design of the study will be a cluster randomised controlled trial at the level of general practices in order to eliminate the influence of contamination of treating patients from both the intervention and control group at the same time. The GP or practice nurse can become more conscious of the treatment process and therefore be stimulated to improve their usual care for the control group as well. The Medical Ethics Committee of the VU University Medical Center in Amsterdam approved the study design, protocols, information letters and informed consent form.

### Setting

Participants will be recruited from general practitioners in the region of Amsterdam and Twente in The Netherlands. A pilot study among diabetes nurses (n = 2) and diabetes patients using insulin (n = 4) from the Diabetes Research Center VUmc in Hoorn has preceded the intervention to test the user friendliness and content of the internet programme. The user friendliness was experienced as good by means that both the nurses and patients were satisfied about the content of the program and were able to use all aspects of the programme easily. They also had the opinion that the program could be used by people not very familiar with using the internet. Only some textual changes in the software were made. The present manuscript can be regarded as the definitive study protocol.

### Study population

The target population consists of T2DM patients (35–75 years) from general practitioners with suboptimal controlled glucose (i.e. HbA1c ≥ 7.0%) and maximal oral hypoglycaemic agents, not using insulin. Inclusion and exclusion criteria are listed in Table 1.

**Table 1 T1:** Inclusion and exclusion criteria

**Inclusion criteria**
• Type 2 diabetes mellitus patients from selected general practices • Between 35 and 75 years • HbA1c ≥ 7.0% in combination with maximal oral hypoglycaemic agents (i.e. the combination of two oral medicines, what cannot further be increased) • Used to a computer and used to the internet • Ability and willingness to inject insulin • Ability and willingness to perform self monitoring of blood glucose • Written informed consent • Understanding of Dutch language
**Exclusion criteria**
• Serious cognitive impairment • Serious other endocrine disorders • Serious disease with a life expectancy < 1 year • Corticosteroid use

### Randomisation and treatment allocation

General practices will be randomly assigned to the intervention or control group using a computerized randomisation programme. In case a practice nurse takes care of the insulin titration (working for one or more general practices), the practice nurse will be randomised and corresponding general practice(s) will be allocated to one of the groups. It is desirable that the two groups will be similar with regard to the amount of patients in each group. For that reason we will apply stratified randomisation [34]. Clusters with one or two general practices and clusters with three or more general practices will be randomised separately. Randomisation will be performed by the manager of the website company (Curavista B.V., Geertruidenberg, the Netherlands), who is independent of the patients and their care. Patients in the intervention group will self-adjust the insulin dose supported by an internet programme and receive education before starting insulin. The control group will receive physician-driven (GP or practice nurse) adjustments, i.e. the GP or practice nurse will perform the insulin titration in his/her own manner, guided by guidelines from the Dutch College of General Practitioners.

When a patient is eligible to participate in our study the GP or practice nurse will provide a letter of invitation and an information brochure of the trial based on the assigned group. The next visit will be scheduled one week later in which the patient can give his or her informed consent to participate in the trial.

The flow of the patients is registered by the investigator (MR), according to a flow diagram recommended by the CONSORT statement and its extended version to cluster randomised trials [35,36]. Reasons for withdrawal are registered by the practice nurse or GP. Figure 1 shows the design of the study.

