### Blinding

It is impossible to blind the participants and health care providers (GP and practice nurse) for the intervention. The investigators will remain blinded during the entire intervention.

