### Study procedure

Approximately 62 GPs (see 'sample size calculation') will be recruited by the principle investigator (MR) and thereafter randomly assigned to the intervention group or control group. Their patients will be allocated to the assigned group.

In the present study, eligible patients will receive insulin glargine. Once-daily injection of a long-acting insulin is attractive, because of the simple dose adjustments based on fasting blood glucose values. It provides at least equivalent glycaemic control to NPH insulin but with a lower incidence of hypoglycaemia [5,25,37]. The GP is free to continue all oral agents, except for thiazolidediones [4].

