### Sample size calculation

The sample size is calculated to detect a clinical relevant difference of 0.5% in HbA1c between groups. In the Diabetes Care System West-Friesland the standard deviation (sd) of HbA1c of the general diabetes population is 1.2% [49]. A difference (d) between the intervention and control group in changes of 0.5%, a standard deviation (sd) of 1.2%, an alpha of 0.05 (two-sided), and a power of 80%, the number of patients requested in each group is 90.

Because cluster randomisation is applied at the level of general practices, the number of patients has to be multiplied with the following formula: 1 + (k-1)ρ, in which ρ is the intercorrelation coefficient (ICC) between practices. The ICC is statistically determined to be 0.05. k is the number of patients per practice that will join the study. Based on our experience, we estimate that 4 patients per practice will make the transition to insulin treatment in one year and meet the criteria of our trial. A participation of 26 general practices is needed per group:

Furthermore, taking into account a possible dropout rate of 15%, the total number of practices needed is: 2 * 26/(1–0.15) = 62, which means that 248 patients will be required.

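### Patients are identified, invited and consented after their practice has been allocated, by unblinded staff using arm-based material, so recruitment can differ between the arms

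*Protocol article*

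**What the plan says.** All references are to the protocol article.

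- **Order of events.** *Study procedure* has about 62 GPs recruited "and thereafter randomly assigned to the intervention group or control group. Their patients will be allocated to the assigned group".
- **Unit randomised.** Under *Randomisation and treatment allocation*, where a practice nurse handles titration, "the practice nurse will be randomised and corresponding general practice(s) will be allocated to one of the groups".
- **Accrual.** Patients are incident cases. Under *Sample size calculation*, "we estimate that 4 patients per practice will make the transition to insulin treatment in one year and meet the criteria of our trial".
- **Invitation.** Once a patient is eligible, "the GP or practice nurse will provide a letter of invitation and an information brochure of the trial based on the assigned group".
- **Consent.** "The next visit will be scheduled one week later in which the patient can give his or her informed consent to participate in the trial".
- **Blinding.** "It is impossible to blind the participants and health care providers (GP and practice nurse) for the intervention". The investigators stay blinded, but they do not invite the patients.
- **Criteria.** Table 1 mixes items that records can settle (age, HbA1c, oral treatment, corticosteroid use) with items that need a judgement, for example "Used to a computer and used to the internet" and being able and willing to inject and to self-monitor.
- **Safeguards stated.** Cluster randomisation is run by a party independent of patient care and stratified by cluster size. There is a CONSORT flow diagram in its cluster version. *Analysis* plans multilevel regression with adjustment, where appropriate, for factors such as age, diabetes duration, medication and education.

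**The concern.** Randomising clusters balances practices, in expectation. It balances patients only if entry into the trial does not depend on the arm. Here every step that decides entry comes after allocation and is taken by someone who knows it.

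Two routes are open. A clinician may read the judgement-based criteria differently when the patient will have to log in and self-titrate than when the practice will do the titration. A patient may also accept or decline according to the care on offer. Either route can leave the arms different in motivation, computer skill or confidence before treatment starts.

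The HbA1c contrast could then partly reflect who was recruited. Self-efficacy, treatment satisfaction and illness perceptions are more exposed, because they are self-reported and lie close to the traits that could drive selection.

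**Working it through.** **Step 1: is recruitment after allocation, by people who know the arm?** No single sentence says that recruiters know their arm. It follows from three statements taken together: practices are randomised before patients are allocated (*Study procedure*), the GP or nurse hands over material based on the arm (*Randomisation and treatment allocation*), and these providers cannot be blinded (*Blinding*). Nobody can hand out arm-based material without knowing the arm. Because patients become eligible over about a year, most cannot have been identified before allocation.

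**Step 2: do the stated safeguards close the gap?**

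| Safeguard | What it does | What remains |
|---|---|---|
| Independent randomisation | Protects allocation of clusters | Does not govern later entry of patients |
| Stratification by cluster size | Balances numbers of patients | Does not address patient type |
| Table 1 in both arms | Fixes age and HbA1c limits | Judgement items can be applied more or less strictly |
| Flow diagram | Counts patients | Describes selection, does not prevent it |
| Prognostic adjustment | Reduces imbalance in measured factors | Cannot remove differences in motivation |
| Design effect | Widens the variance for clustering | Does not remove bias |

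The limitations in *Discussion* cover varying usual care and co-medication, not differential recruitment.

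**Step 3: the plan's own figures.** With a difference of 0.5, SD 1.2, two-sided alpha 0.05 and 80% power:

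- n per group = 2 × (1.960 + 0.842)² × 1.2² / 0.5² = 90.4; the plan states 90.
- Design effect = 1 + (4 − 1) × 0.05 = 1.15.
- Practices per group = 90 × 1.15 / 4 = 25.9, so 26.
- Total practices = 2 × 26 / 0.85 = 61.2, so 62; patients = 62 × 4 = 248.

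The sample size reproduces, and the point does not depend on it.

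**Step 4: how sensitive would the test be?** The documents give no figure for the bias. Let b be an *assumed* shift in the between-arm difference in HbA1c change caused by recruitment alone. Effective n per arm = 124 × 0.85 / 1.15 = 91.7. Standard error = 1.2 × √(2 / 91.7) = 0.177.

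- Type I error with no true effect = Φ(b/SE − 1.96) + Φ(−b/SE − 1.96).
- Power for 0.5 if the bias runs against the programme = Φ((0.5 − b)/SE − 1.96).

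| Assumed b (% HbA1c) | Type I error | Power for 0.5 if bias is adverse |
|---|---|---|
| 0 | 0.050 | 0.805 |
| 0.05 | 0.059 | 0.719 |
| 0.10 | 0.087 | 0.617 |
| 0.20 | 0.204 | 0.395 |
| 0.30 | 0.395 | 0.203 |

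The table shows what a given bias would do. It is no estimate of the bias.

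**The case against.** Recruitment after allocation is common where cases are incident and clusters are used to avoid contamination, which is the reason the article gives. The document shows a risk, not an occurrence. That stands, and it limits how strongly the point can be put.

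Four stronger readings are tempting, and the document does not support them:

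- **That the plan relies on flow-chart counts alone.** *Analysis* provides for prognostic adjustment and looks at age, depression and previous internet use as effect modifiers. Internet experience, depression, self-efficacy and insulin perceptions are recorded at baseline. The adjustment list is open-ended, so leaving baseline HbA1c unnamed is not in itself an error.
- **That control practices may invite anyone about to start insulin.** Table 1 applies to both arms, and control patients also complete web questionnaires. Only the strictness with which the criteria are applied can differ.
- **That each brochure describes one arm only.** The text says the brochure is based on the assigned group. The brochure is not shown, and the other arm may be described in it.
- **That the bias has a known size or direction.** Any figure for a baseline HbA1c imbalance would be assumed. It would also concern a measured variable that regression can adjust for, whereas the main worry is motivation.

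It is also fair to say that no pre-allocation list can cover patients who become eligible later.

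**Conclusion.** The concern holds as a design weakness. The stated procedure permits clinician selection and patient consent to differ by arm, and this follows from what the article says, not from detail left to a fuller document. The common criteria and the planned adjustment reduce the problem but do not close it, and the article does not acknowledge it as a limitation.

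Size and direction are not derivable. The sensitivity table rests on the plan's SD, ICC and dropout and on assumed values of b. It shows only that a shift of 0.10 to 0.20, well below the 0.5 target, would matter. The document does not show that such a shift occurred. This is worth an inexpensive improvement in recruitment and reporting. It is no reason to redesign the trial.

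**What to change.** 1. In every practice, run the same register search on the record-checkable Table 1 criteria. Do it before allocation is disclosed where that is still possible (the trial began in January 2009), and at fixed intervals afterwards for new cases.
2. Invite all listed patients. Apply the judgement-based criteria only after listing, and log the reason for each exclusion.
3. Use the same core description of the trial in both arms' invitation material.
4. Report listed, invited and consenting patients by arm and cluster, with anonymised age, sex and HbA1c of those not invited or declining.
5. Name baseline HbA1c, with previous internet use, as an adjustment covariate.
6. State the residual risk as a limitation.

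**Cost.** Periodic register queries and a short log per practice, plus an ethics notification. If the interval were quarterly, that would be four searches per practice a year, or 62 × 4 = 248 across the trial. No extra staff should be needed. Bias for cases arising after disclosure is reduced, not removed, and adjustment will not recover differences in motivation.
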